## Abstract

**Trial registration:**

ClinicalTrials.gov NCT06538142

## Introduction

Molar-Incisor Hypomineralization (MIH) is a developmental enamel defect that impairs mineralization during the amelogenesis process, primarily affecting the first permanent molars and, in some cases, the incisors [1]. Molar-Incisor Hypomineralization (MIH) is characterized by well-defined, asymmetrical opacities with varying color shades. Darker opacities exhibit a higher susceptibility to fractures due to a greater compromise in their mineral composition [1]. MIH poses a significant clinical challenge due to dental hypersensitivity, an increased risk of caries, and difficulties in achieving adequate adhesion of restorative materials [2].

Hypersensitivity is a common symptom in patients with MIH and may occur in teeth with or without post-eruptive fractures. The severity of clinical manifestations is directly correlated with the intensity of hypersensitivity [3]. Although the underlying mechanisms of hypersensitivity in MIH-affected teeth are not yet fully elucidated, it is hypothesized that chronic stimuli contribute to a subclinical pulpal inflammation. This process is likely driven by bacterial infiltration through the porous enamel, leading to persistent nociceptive responses [4].

Photobiomodulation with low- or high-power laser is a potential treatment method for dentinal hypersensitivity [5]. Photobiomodulation (PBM) with low-level laser (LLL), such as GaAlAs or He-Ne, has no known side effects when administered with the appropriate settings. The mechanism of action is based on the induction of changes in nerve transmission to control pain. Nerve cells are stimulated and the sodium/potassium pump in the cell membrane increases the amplitude of the action potential, thus blocking the transmission of the pain stimulus. Moreover, PBM enhances cell regeneration capacity and reduces inflammation [6,7].

Teeth affected by Molar-Incisor Hypomineralization (MIH) exhibit a reduction in mineral content, accompanied by an increase in organic content due to the retention of proteins during the mineralization process. This structural modification compromises the adhesion of restorative materials to the hypomineralized enamel, making it one of the main factors associated with the failure of restorative procedures. As a result, there is a higher failure rate in treatments, often requiring re-treatments and restorative replacements over time. [8,9].

The preferred approach for teeth with MIH and post-eruptive fractures is restorative treatment with or without absolute isolation. Relative isolation has been shown to be effective in MIH teeth restored with hybrid glass materials [10]. Moreover, some studies have not observed significant differences in the longevity of resin restorations when comparing relative and absolute isolation methods [10–13].

Stela composite resin (Southern Dental Industries) is an innovative, high-performance, self-cure composite with a catalyst that initiates the curing process at the restoration interface. The polymerization sequence attenuates contraction tension by enabling an interface with no gaps, reducing postoperative sensitivity and the risk of premature failure [14–19]. This product has a simple process and fast execution, which is particularly beneficial for children with MIH. There is a need for the investigation of procedures aimed at reducing hypersensitivity and materials that can enhance the longevity of restorations, especially on teeth affected by MIH to improve clinical outcomes, minimize the need for additional interventions and enhance the quality of life of patients.

Therefore, the aim of the proposed study is to determine whether photobiomodulation combined with a new photopolymerizable resin improves hypersensitivity in MIH-affected carious molars. The secondary objectives are to evaluate the effectiveness in controlling hypersensitivity over time and to assess the clinical performance of the self-cure composite resin in terms of restoration longevity.

## Methods

### Study design

A randomized, controlled, single-blinded clinical trial will be conducted. The present protocol study followed the Standard Protocol Items for Randomized Trials (SPIRIT statement), as presented in Fig 1 and S1 File (SPIRIT checklist). The recruitment and data collection period will take place between February 1, 2025, and January 1, 2026. The results are expected to be available by August 2026. The clinical trial protocol is provided as Supporting Information file (S2 File).

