### Description of sample

Teeth will be selected from male and female children 6–10 years of age with no distinction as to ethnicity enrolled for outpatient treatment at the Aria College in the city of Brasília with first molars that have MIH and restorative treatment need. The study has received a letter of approval from Aria College, granting permission for the research to be conducted in the Department of Pediatric Dentistry at their facility. Individuals who met the eligibility criteria will immediately be randomized and treated. Each participant will receive treatment on a single molar affected by MIH. In cases where more than one tooth meets the eligibility criteria, the tooth to be included in the study will be selected randomly through a simple lottery method. This selection process will occur prior to the randomization of the interventions to ensure a clear and unbiased allocation of treatments. The trial will be reported following the CONSORT guidelines.

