### Sample size calculation

The sample size will be estimated using the G*Power software (version 3.1, Franz Faul, Unikiel, Germany) [22] for a priori repeated measures ANOVA. An effect size of 0.352, derived from the group mean dispersions reported in the literature [23], will be considered. The alpha error will be set at 0.05, statistical power at 80%, and the design includes 3 groups and 5 repeated measures. The final calculation indicates the need for 66 individuals in total, corresponding to 22 participants per group. To increase the robustness of the results and compensate for potential dropouts, the sample will be inflated by 15%, resulting in 25 individuals per group and a total of 75 participants.

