### Blinding

All treatments across the three groups will be carried out by a single operator, who will have completed training and calibration sessions during the initial phase of the study. Clinical assessments after 48 hours as well as four, eight and twelve months after treatment (follow-up) will be performed by an examiner blinded to allocation (single-blind study). The operator and examiner will undergo previous calibration exercises, evaluating approximately 20 cases, with the calculation of the Kappa statistic to ensure greater than 85% inter-observer agreement. The calibration will follow the criteria of the modified index of the United States Public Health Service (USPHS) [24,25] and the MIH-SSS diagnostic criteria [20]. The data will be analyzed by a blinded statistician.

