### Clinical protocol

#### Group 1 – photobiomodulation + restoration with self-cure composite resin.

Initial periapical radiograph;Hypersensitivity reading (Wong-Baker Faces Pain Rating Scale for subjective pain of volunteer and SCASS for examiner’s assessment);Application of photobiomodulation;Relative isolation (lip bumper, cotton roll and aspirator);Selective removal of carious tissue with excavator, which involves complete removal of carious dentin from the surrounding walls followed by partial removal of softened dentin from the pulp wall (only Code 6 of MIH-SSS criteria);Cleaning with cotton and water;Application of primer (Stela; SDI, Melbourne, Vic, Australia) on dentin and/or enamel, wait 5 seconds;Application of mild compressed air on adhesive for 3 seconds;Restoration with self-cure composite resin (Stela; SDI, Melbourne, Vic, Australia) extending to adjacent demarcated opacities;Clinical follow up after 48 hours and at four-month intervals for a period of 12 months (modified USPHS index);Hypersensitivity reading after 48 hours and at four-month intervals for a period of 12 months (Wong-Baker Faces Pain Rating Scale for subjective pain of volunteer and SCASS for examiner’s assessment).

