#### Hypersensitivity assessment.

Pain perception in children was evaluated through the Wong-Baker Faces Pain Rating Scale [29] and the Schiff Cold Air Sensitivity Scale (SCASS) [30] will be used for the assessment of the operator and examiner. Following isolation of the neighboring teeth with gauze, compressed air will be applied to the tooth with MIH for three seconds. The SCASS is scored as follows: 0 (no reaction); 1 (no reaction, but patient reports discomfort); 2 (patient reacts and moves away from stimulus); and 3 (patient reacts and asks operator to stop) [3]. Hypersensitivity will be measured using the Wong-Baker Faces Pain Rating Scale and SCASS prior to the procedure, 48 hours after restorative treatment and at four-month intervals for the 12-month follow-up period.

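### The stated 11-month period for recruitment and data collection cannot contain any participant's 12-month reading, so the dates and the follow-up schedule must be reconciled

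*Protocol article*

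**What the plan says.** The Study design section of the protocol article gives one period for two activities: "The recruitment and data collection period will take place between February 1, 2025, and January 1, 2026". It adds: "The results are expected to be available by August 2026".

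The follow-up schedule is tied to treatment, not to the calendar. Under Blinding: "Clinical assessments after 48 hours as well as four, eight and twelve months after treatment (follow-up) will be performed by an examiner blinded to allocation". Under Hypersensitivity assessment, the two pain scales are read "prior to the procedure, 48 hours after restorative treatment and at four-month intervals for the 12-month follow-up period". The Clinical protocol lists the same readings for Group 1 ("Hypersensitivity reading after 48 hours and at four-month intervals for a period of 12 months"), carries them over to Group 2 by reference, and repeats them for Group 3.

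Treatment follows enrolment without delay, according to Description of sample: "Individuals who met the eligibility criteria will immediately be randomized and treated".

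The Sample size calculation assumes that "the design includes 3 groups and 5 repeated measures". The Statistical analysis section plans a repeated measures ANOVA of three groups over five times.

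**The concern.** The stated period is shorter than one participant's follow-up. Month 12 is not an optional extra reading here. It is the fifth of the five measurements behind the sample size and the repeated measures ANOVA, and it closes the follow-up on which restoration longevity is judged.

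If the stated dates were applied literally, the fifth time point would be empty. A classical repeated measures ANOVA uses participants who have every time point, so the planned five-time analysis would have no complete cases. If the dates were instead taken as recruitment only, the expected results date could arrive while some children were still in follow-up.

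**Working it through.** **Inputs, all from the protocol article**

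- Period: 1 February 2025 to 1 January 2026 (Study design).
- Expected results: August 2026 (Study design).
- Readings: before treatment, 48 hours, then 4, 8 and 12 months after treatment (Blinding, Clinical protocol, Hypersensitivity assessment).
- Delay from enrolment to treatment: none (Description of sample), so the earliest treatment date is 1 February 2025.
- Sample: 66 needed, 75 planned (Sample size calculation).

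**1. The plan's own count of time points.** Baseline, 48 hours, 4, 8 and 12 months make 5. This agrees with the sample size and the analysis, and it is reached only if month 12 is observed.

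**2. Length of the period.** 1 January 2026 minus 1 February 2025 = 334 days = 11 calendar months.

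**3. Which visits fit.** Earliest visit = start date + m months. Latest treatment date that still fits = end date − m months.

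| Visit | Earliest possible visit | Treatment needed by, to fit before 1 January 2026 |
|---|---|---|
| 4 months | 1 June 2025 | 1 September 2025 |
| 8 months | 1 October 2025 | 1 May 2025 |
| 12 months | 1 February 2026 | 1 January 2025 |

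The 12-month row requires treatment one month before recruitment opens. The earliest 12-month reading falls 31 days after the stated end (1 January to 1 February 2026). The number of participants who can have it inside the period is 0 of 75, with no assumption about accrual.

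**4. The 4- and 8-month readings.** These depend on accrual, which the article does not give.

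- Uniform accrual over the 11 months (assumption): 8-month reading 3/11 = 27%; 4-month reading 7/11 = 64%.
- All children treated by about 1 May 2025 (assumption): 100% for both.
- Later accrual than uniform would give less than 27% and 64%.

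**5. Period read as recruitment only.** Last treatment 1 January 2026 + 12 months = 1 January 2027, which is after August 2026. For a 12-month visit to fall by 1 to 31 August 2026, treatment must be by 1 to 31 August 2025, which is 181 to 211 days after the start. Under uniform accrual (assumption) that covers 181/334 = 54% to 211/334 = 63% of children, or about 41 to 47 of 75, with no time left for cleaning or analysis. The calculated need is 66.

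**6. Recruitment closed early, follow-up into 2026.** Treating all 75 children between 1 February and 1 August 2025 means 75/6 = 12.5 per month, against 75/11 = 6.8 per month over the full period. All 12-month visits would then be done by 1 August 2026, again with no allowance for analysis. This reading can meet the results date if recruitment closes somewhat earlier still, but it contradicts the stated end of data collection.

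**The case against.** The strongest reply is that the calendar sentence is a slip. Every operative rule is anchored to treatment, five time points are stated consistently, and nothing in the article says that visits stop or that the database closes on 1 January 2026. The timeline figure and the full protocol, supplied as a supporting file, are not shown and may separate the dates properly. Correcting the sentence leaves allocation, outcomes, sample size and model as they are.

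Much of this stands, and it limits the point. It does not remove it, because no section that can be read resolves the conflict, and other dates elsewhere would not make this sentence agree with the schedule.

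A reader might go further and infer any of the following. The documents do not support them:

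- *The investigators intend to skip the 12-month visit.* The schedule sections all require it. An empty fifth time point follows only from applying the dates literally.
- *The 8-month reading would be mostly missing.* That holds under uniform accrual. With all children treated by about 1 May 2025 none would be missing.
- *Results will be analysed before follow-up is complete.* August 2026 is an expectation, not a commitment, and recruitment that closed early in 2025 could meet it.
- *The registry entry is wrong too.* The registry record is not available here, so its dates cannot be judged.

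**Conclusion.** The concern holds as a contradiction between dates and schedule. The stated period is 334 days, a 12-month reading cannot fall inside it, and 0 of 75 participants can have one there. This rests only on the article's own dates, its visit schedule and its statement that treatment follows enrolment at once.

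Reading the period as recruitment only does not reconcile the text: it disregards the mention of data collection, and it allows 12-month visits up to about 1 January 2027, past the expected results date. Early closure of recruitment with follow-up into 2026 would be feasible, but it is not stated and still needs a different data-collection end. On every reading at least one stated date has to change.

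The figures for the 8- and 4-month readings (27% and 64% under uniform accrual, up to 100% under early accrual) are conditional and are not part of the core finding. No fault in the choice of endpoint, design or model is shown.

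**What to change.** In the Study design section:

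1. State the end of recruitment and the end of data collection as two separate dates, with data collection ending no earlier than 12 months after the last treatment.
2. Choose one of two courses for the results date. Either move it to after the last 12-month visit plus time for analysis, or keep August 2026 and set a recruitment end early enough in 2025 that every 12-month visit and the analysis come before it.
3. Check that the timeline figure, the supporting protocol file and the registry entry carry the same dates.

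The change itself is an edit to a few dates. Its real cost is either later results (a last 12-month visit around 1 January 2027 if recruitment runs to 1 January 2026) or faster recruitment (more than 12.5 children per month to leave room for analysis before 1 August 2026, instead of about 6.8). Allocation, outcomes, sample size and the planned model need no change on this account.

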**Fig 1 pone.0329641.g001:**
[figure not shown]
Timeframe of enrolment, intervention and assessments.

### Ethical aspects

The study will be conducted in accordance with the ethical precepts stipulated in the Declaration of Helsinki (World Medical Association, 2008) and the norms governing research involving human beings stipulated in Resolutions nº 466/12 and 510/2016 of the National Board of Health. The study received approval from the Human Research Ethics Committee of Nove de Julho University (certificate number: 83027624.2.0000.5511/approval date: December 4, 2024) and was registered in ClinicalTrials.gov (NCT06538142, Last Update: January 17, 2025). The legal guardians will agree to the children’s participation by signing a statement of informed consent. Recruitment will begin after approval from the Human Research Ethics Committee. The participants will be informed that they can withdraw from the study at any time for any reason, if they so desire. The researchers may withdraw participants from the study if it is considered necessary.

### Objectives

Primary Objective: To determine whether photobiomodulation combined with a new photopolymerizable resin improves hypersensitivity in MIH-affected carious molars.

Secondary objectives:

To compare the effectiveness of three interventions: photobiomodulation combined with self-cure resin, self-cure resin alone, and photobiomodulation combined with bulkfill photopolymerizable resin in controlling hypersensitivity over time.To assess the clinical performance of the self-cure composite resin in terms of restoration longevity.

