### Randomization

The participants will be randomly allocated to the different groups using block randomization. A computer-generated sequence (random.org; Randomness and Integrity Services, Dublin, Leinster, Ireland) will be used to allocate each participant to a specific group maintaining a 1:1:1 proportion (equal number of participants in all groups). Randomization will be performed in 5 blocks, with 15 participants per block, totaling 75 participants across the study. Allocation concealment will be ensured with the use of sequentially numbered sealed opaque envelopes.

Teeth selected for treatment will be randomized into three groups:

**Group 1**: Photobiomodulation + restoration with self-cure composite resin

**Group 2**: Restoration with self-cure composite resin

**Group 3**: Photobiomodulation + restoration with photopolymerizable bulk-fill composite resin

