### Statistical analysis

The data will be presented using descriptive statistics. Continuous variables will be described with mean and standard deviation, and categorical variables by relative frequency. Statistical analyses will be conducted using SPSS software (version 28.0, IBM, USA). For comparisons of the Wong-Baker Faces Pain Rating Scale and SCASS scales, a repeated measures analysis of variance (ANOVA) will be used, considering the three groups and five time points of the study. This analysis will address the objective of comparing the effectiveness of interventions in controlling hypersensitivity over time. Post-hoc comparisons will be made using the Bonferroni adjustment to control for Type I error in multiple comparisons. The normality of the data distribution and the homogeneity of variance will be confirmed by the Shapiro-Wilk and Levene tests, respectively. The presence of sphericity will be verified using the Mauchly test, and if violated, corrections such as Greenhouse-Geisser will be applied. For secondary outcomes, repeated measures ANOVA will also be used to compare differences over time among the three intervention groups. Post-hoc analyses with Bonferroni correction will be applied when necessary. Effect sizes (partial eta squared) will be reported to assess the magnitude of differences between interventions. Additionally, Pearson or Spearman correlation coefficients will be used to explore associations between changes in hypersensitivity and secondary outcomes, depending on data distribution. Sensitivity analyses using an intention-to-treat approach may also be performed to assess the robustness of the findings. A significance level of 0.05 will be adopted for all analyses.

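### The primary objective names a new photopolymerizable resin, but the new resin is self-cure and the photopolymerizable one is never given without laser, so the objective matches no randomised contrast

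*Protocol article*

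**What the plan says.** All references are to the protocol article.

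- **Objectives:** the section opens with "Primary Objective: To determine whether photobiomodulation combined with a new photopolymerizable resin improves hypersensitivity in MIH-affected carious molars". It names no comparator. The Introduction closes with the same aim: "determine whether photobiomodulation combined with a new photopolymerizable resin improves hypersensitivity in MIH-affected carious molars".
- **Introduction:** the only resin presented as new is Stela, which "is an innovative, high-performance, self-cure composite with a catalyst that initiates the curing process at the restoration interface".
- **Randomization:** Group 1 is laser plus self-cure resin, and Group 2 is self-cure resin alone. Group 3 is "Photobiomodulation + restoration with photopolymerizable bulk-fill composite resin". The clinical protocol defines Group 2 as the Group 1 sequence without the laser step.
- **Objectives, secondary:** the comparison of the three interventions over time is listed here, with each resin named correctly.
- **Statistical analysis:** a repeated measures ANOVA (three groups, five time points) is applied to both the Wong-Baker scale and the SCASS, with Bonferroni-adjusted post-hoc comparisons. The section says that this analysis serves the comparison of the interventions over time. It ends: "A significance level of 0.05 will be adopted for all analyses".
- **Inclusion criteria and clinical protocol:** MIH-SSS codes 5 and 6 are both eligible. Removal of carious tissue is marked "only Code 6 of MIH-SSS criteria".

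**The concern.** The primary objective decides what the trial may claim. Here it describes a treatment combination (laser plus a resin that is both new and photopolymerizable) that no arm receives. If the word photopolymerizable is taken at face value, the objective points to Group 3, for which there is no laser-free counterpart. If the word new is taken at face value, it points to Group 1. A reader cannot tell from the objective which arms decide success.

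The analysis text does not settle it. The ANOVA is expressly tied to an objective listed as secondary, two scales stand on an equal footing, and neither the group effect nor the group-by-time interaction is singled out. The scale and the effect that carry the conclusion could therefore be chosen once results are known. The stated 80% power also says nothing direct about the laser question, because the sample size is for the three-group design.

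**Working it through.** **1. Arms against objective.**

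| Arm | Laser | Resin |
|---|---|---|
| Group 1 | yes | self-cure (Stela, the new product) |
| Group 2 | no | self-cure (Stela) |
| Group 3 | yes | photopolymerizable bulk-fill |
| no such arm | no | photopolymerizable bulk-fill |

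**2. What each randomised contrast estimates.**
- Group 1 vs Group 2: the laser effect when the self-cure resin is used.
- Group 1 vs Group 3: the restoration system (resin together with its bonding procedure), with laser in both arms.
- Group 3 vs Group 2: laser, resin and bonding procedure all change at once, so the effects are confounded.
- Laser effect with the photopolymerizable resin: not estimable, because the fourth cell is empty. A before-after change within Group 3 would be uncontrolled.

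So the objective as worded has no contrast. With self-cure in place of photopolymerizable, it has a clean one.

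**3. Error over two scales.** Each scale is tested at 0.05. If the tests were independent, the chance of at least one false positive is 1 − 0.95² = 1 − 0.9025 = 0.0975, about 9.8%. Both scales rate the same child at the same visits, so they will be positively correlated and the true figure lies between 5% and 9.8%. The Bonferroni adjustment applies to post-hoc comparisons. It does not cover the choice of scale, or of group effect versus interaction.

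**4. What the 80% power refers to.** Inputs from Sample size calculation: f = 0.352, alpha 0.05, 3 groups, 5 measures, N = 66. The correlation ρ between measures is not stated, so a range is shown. For the between-group test in repeated measures ANOVA:

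λ = f² × N × m / (1 + (m − 1)ρ), with 2 and 63 degrees of freedom and critical F = 3.143.

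At ρ = 0.75: λ = 0.1239 × 66 × 5 / 4 = 10.22, giving power 80.5%.

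| Assumed ρ | Power at N = 66 | Smallest N (multiple of 3) for 80% |
|---|---|---|
| 0.5 | 90.8% | 51 |
| 0.7 | 82.6% | 63 |
| 0.75 | 80.5% | 66 |
| 0.8 | 78.4% | 69 |

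The group-by-time interaction would need 27 or fewer in total (36 under the SPSS effect-size option). The figure of 66 therefore fits the three-group between-subject test with ρ near 0.75. It is not a calculation for Group 1 versus Group 2.

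**5. The word carious.** The objective restricts the question to carious molars, while enrolment takes codes 5 and 6 and the protocol removes carious tissue only in code 6. Caries is not an inclusion criterion. The code definitions sit in a cited source that is not at hand, so this is a mismatch of wording and not proof that code 5 teeth are free of caries.

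**The case against.** The best defence is that this is a slip of one word. Only one resin is called innovative, the secondary objectives name all resins correctly, and the intended meaning is easy to recover. That stands as far as the design goes. A reader might infer that the trial cannot answer its primary question, or that a bulk-fill arm without laser is missing. The documents do not support this: once self-cure is restored, Group 1 versus Group 2 answers the laser question. But the same wording appears in two sections, one of them the formal statement of the primary objective, so it still has to be corrected.

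Second, the planned post-hoc comparisons already separate laser from restoration system, and Bonferroni covers the choice among pairs of arms. That also stands. What stays open is the scale and the effect tested.

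Third, the Statistical analysis section goes on to say that the same method will also be used for secondary outcomes, which implies that hypersensitivity is primary. This is fair. The outcome domain can be inferred, but the scale and the contrast cannot.

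Fourth, the full protocol is cited as a supporting file and an analysis plan may exist, and either could name the scale and contrast. For that reason the unnamed contrast carries less weight than the contradiction, which is on the face of the article.

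A reader might also want a power figure for Group 1 versus Group 2. The documents do not support one. It would depend on the unstated correlation, on which arms are assumed to differ, and on whether an effect is wrongly assumed at the pre-treatment visit.

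**Conclusion.** The point holds as an internal contradiction in the primary objective, not as a fault of the design. The objective in the Objectives section and in the Introduction describes a new photopolymerizable resin that is in no arm. Read literally, it has no randomised contrast. The arms as randomised can answer the evident question through Group 1 versus Group 2.

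The open choice of scale is a smaller matter. It raises the false-positive chance from 5% to at most 9.8%, a bound that assumes independent scales. The statement that the 80% power belongs to the three-group test rests on an assumed correlation near 0.75, which the article does not give. The mismatch over carious teeth is supporting only.

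**What to change.** 1. In both the Introduction and the Objectives, reword the primary aim as photobiomodulation plus self-cure resin compared with self-cure resin alone. Describe the population as the enrolled MIH-SSS code 5 and 6 molars, or otherwise reconcile the word carious with the inclusion criteria.
2. In Statistical analysis, name one primary contrast: Group 1 versus Group 2 on one chosen scale at 0.05. Define it as the between-group difference over the four post-treatment visits (48 hours and 4, 8 and 12 months), adjusted for the baseline score. This settles the choice between group effect and interaction, and it keeps the pre-treatment visit, where randomised arms have no expected difference, from diluting the effect.
3. Make Group 1 versus Group 3, the other scale and single-visit comparisons secondary.
4. In Sample size calculation, say that the 80% refers to the three-group test and state the correlation used.

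The cost is wording in the protocol, and in the registry entry if it carries the same text. No arm, participant or visit is added. The change should be dated and made before any unblinded analysis.
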